### Study Setting

The study will be conducted in rural districts of two states in India: Jhajjar (Haryana) and Guntur (Andhra Pradesh). Haryana is a state in northern India, whose history of significant gender inequity (21), has improved over the last decade due to targeted legislation and policies, as well as community-based action groups. Andhra Pradesh is a state in south-eastern India with high rates of diabetes and hypertension in the adult population (22). The two states are geographically and culturally diverse, with unique languages, cuisine and practises. The maternal mortality ratio is 101/100,000 births in Haryana, and 74/100,000 births in Andhra Pradesh (23). In the National Family Health Survey IV (24), total prevalence of hypertension and diabetes in women of reproductive age was 10.1% in Andhra Pradesh, and 9.2% in Haryana. Prevalence of raised blood sugar indicative of diabetes in women of reproductive age in Andhra Pradesh and Haryana was 13.1 and 6.6%, respectively (24).

### Sampling

A list of PHCs in each district will be compiled using data from Government of India State websites (25, 26). The PHCs will be stratified by geographic region and population size (each PHC to serve a population above 30,000) to include: up to eight primary care doctors (two at each PHC cluster), up to 20 ANMs (five at each cluster), and 80 ASHAs (20 at each cluster). The villages selected under each intervention and control PHC will be non-contiguous to avoid contamination. Each PHC will be assessed for eligibility (see below). Consent for the PHC and its staff to participate in the study will be obtained from the administrative lead at each eligible PHC prior to randomisation. Please see Table 1 for the study inclusion criteria.

**Table 1 T1:** Summary of inclusion criteria for the study.

**Inclusion criteria** • Primary Health Centres (PHCs) serving a population of 30,000 people or more, in either the: (a) Jhajjar district of Haryana or (b) Guntur district of Andhra Pradesh. • Primary care doctors working at the participating PHCs, in either (a) Jhajjar district of Haryana or (b) Guntur district of Andhra Pradesh. • Community Health Workers (ANMs and ASHAs) working in partnership with the participating PHCs, in either (a) Jhajjar district of Haryana or (b) Guntur district of Andhra Pradesh. • Pregnant women above the age of 18 years (adults) living within the villages in the catchment area of the PHCs participating in the study, in either (a) Jhajjar district of Haryana or (b) Guntur district of Andhra Pradesh. ^*^PHCs and participants not meeting the above criteria will be excluded from the study

### Randomisation

Randomisation will be at the PHC cluster level, as individual randomisation would not be possible due to potential contamination. Four PHCs (including the villages affiliated to each PHC) will be allocated centrally to the SMARThealth Pregnancy intervention or control group (enhanced standard care), using a simple random number generator. This process will be overseen by a statistician at The George Institute for Global Health (TGIGH), blinded to the PHCs.

### Participants

We will recruit 200 pregnant women (50 in each of the four PHC clusters) from the two districts. Participants will be ≥18 years old (adults), between 28 and 36 weeks' gestation, and followed up until and including 6 weeks postpartum. The last trimester of pregnancy was chosen to recruit participants as the contextual study (14) revealed women migrated to their mother's homes prior to delivery. We wanted to ensure these women were connected to health services after migration and received postpartum follow-up. After discussion with a statistician at TGIGH (LB), four clusters from two different districts recruiting a total of 200 pregnant women were considered pragmatic to provide rich feasibility data, as well as early estimates of clinical outcomes. As the focus of this pilot study is to assess the feasibility and acceptability of conducting a definitive trial, no formal sample size calculation was undertaken.

### Recruitment and Consent

Eligible pregnant women will be identified by the ANM during their standard antenatal care visits. The ANM will inform the locally-based research assistant from TGIGH, India, of eligible participants. The research assistant will then obtain informed consent to participate in the study.

Women in the intervention group will be asked to consent to having their BP and Hb measured by an ASHA at three time points during: (a) the last trimester of pregnancy (between 28 and 36 weeks gestation); (b) week 1 postpartum and (c) week 6 postpartum. They will also consent to sharing their antenatal care handheld record containing their demographic details, medical and obstetric history, and details of all their previous BP and Hb readings. In addition, they will consent to having their BP and Hb measured at home by an independent member of the research team at the baseline of the study, and after the final 6 week postpartum visit (see Figure 1).

**Figure 1 F1:**
[figure not shown]
Participant flowchart of pilot study.

Women in the control group will be asked to consent to sharing their antenatal care handheld record, containing their demographic details, medical and obstetric history, and details of all their previous BP and Hb readings from their antenatal visits. In addition, they will consent to having their BP and Hb measured at home by an independent member of the research team at the baseline of the study, and after their routine 6 week postpartum visit. Individual consent will be sought from CHWs and doctors prior to interviews and FGDs.

## The SMARThealth Pregnancy intervention

The SMARThealth Pregnancy intervention includes two components:

A targeted educational and training component for CHWs on anaemia in pregnancy, HDP and GDM.An mHealth platform providing clinical decision support and lifestyle advice for ASHAs and primary care doctors.

The intervention will be delivered in three stages: (1) Education and Training; (2) Delivery of the mHealth Intervention and (3) End of study assessment (see Figure 2).

**Figure 2 F2:**
[figure not shown]
Stages in SMARThealth pregnancy study.

### Stage 1: Education and Training

A train the trainers programme has been developed for all study staff on the importance of identifying women with a high-risk pregnancy; detecting anaemia, HDP and GDM antenatal and postnatally, and the impact of these conditions on the life-long health of women. The programme also outlines the delivery of the standardised training for CHWs.

The training curriculum for CHWs has been designed to build upon existing CHW training on high-risk pregnancies, and cover key learning objectives in relation to the importance of identification of high-risk pregnant women, with a focus on detection, referral and management of HDP, GDM, and anaemia in pregnancy according to established clinical guidelines (27–31). CHWs will also be taught how to use the SMARThealth Pregnancy mHealth mobile tablet, and provided information on what to do if the technology does not work properly. They will additionally learn the following skills:

Measuring BP using the CRADLE VSA Blood Pressure Monitor (APEC, UK) (32) and interpreting the readings. The CRADLE device is a low-cost semi-automated BP device, specifically designed for low resource settings, charged using an android phone charger, and has been used by CHWs in India (31).Measuring Hb using the handheld TrueHb Hemometer (Wrig nanosystems Pvt. Ltd., 2020) (33) and interpretation of readings.Communication of findings and concerns by ASHA to ANM/primary care doctor, and skills in handover of care between health professionals.

Training will be delivered to ASHAs and ANMs in a series of five participatory learning sessions each of 3-h duration conducted over two and a half days, with a 1-day face-to-face refresher training session after 4 weeks. In between the two training sessions, there will be “hand-holding” in the field by the local study field team, to ensure the ASHAs feel confident using the blood pressure device, haemoglobinometer and the tablet device (see below).

The curriculum for primary care doctors will cover the same areas as for CHWs, however the delivery will be over a half-day of one-to-one training, assuming a degree of baseline knowledge on both educational and training components.

### Stage 2: The SMARThealth Pregnancy mHealth Platform

The SMARThealth Pregnancy mHealth platform is a smartphone-based application, using an Android operating system, on a seven inch mobile tablet. The application is multi-faceted and includes provision of clinical decision support for ASHAs and primary care doctors regarding interpretation of BP, Hb and blood sugar measurements, grading of severity and appropriate referral information using established clinical guidelines (27–31). Mobile tablets will be provided to ASHAs working in the villages, and to the primary care doctor at the corresponding PHC.

In addition to standard antenatal and postnatal visits, ASHAs in the intervention group will visit the pregnant woman enrolled in the study at home, and perform BP readings, and take a finger-prick Hb test at three different time points:

Once during the last trimester of pregnancy between 28 and 36 weeks' gestation.At 1–2 weeks postpartumAt 6 weeks postpartum

The SMARThealth Pregnancy mHealth platform will have options for the ASHAs to enter the input measurements to generate recommendations based on the woman's history, BP, Hb and blood glucose readings, which will be confidentially uploaded to a patient record using Open MRS software (34) and synchronise to a sister-tablet held by the primary care doctor at the local PHC. All recommendations are based on established country-specific clinical guidelines. Women will be referred to the doctor at the local PHC via the mHealth platform, and provided with a paper referral card. Although women cannot be compelled to see the primary care doctor, they will however be encouraged to attend the PHC after each ASHA visit. The ASHA will accompany the woman for the visit to the primary care doctor or to secondary care as per current standard practise.

Through the SMARThealth Pregnancy mHealth platform, the primary care doctor will be able to note if the woman is anaemic (and the severity), hypertensive, and/or screen-positive for GDM. The primary care doctor will be guided to repeat these readings if the patient attends the PHC, with access to guideline-based decision support for anaemia, hypertension and GDM as to the next steps in management/and or referral to secondary care. Priority patients (identified to have high-risk pregnancy conditions, and/or outstanding investigations), will have a red traffic light alert and be automatically placed at the top of the priority list when the SMARThealth Pregnancy application is launched on the ASHA and primary care doctor tablets.

Postnatal visits take the same course as the antenatal visit, except the history-taking will involve details of the birth and labour (Postpartum: Week 1 visit), and any further complications (Postpartum: Week 6 visit).

To ensure quality assurance for intervention practises, regular field visits and observations of ASHAs and primary care doctors will be made by the research team and project managers at each study site to ensure compliance to study procedures and the fidelity of the intervention practises. In addition, data collected through the mHealth tablets will be used to monitor visits made and completed by ASHAs and primary care doctors.

### Control Group

The control group will receive *enhanced standard* antenatal and postnatal care, involving: An awareness programme for pregnant women, CHWs and primary care doctors, conducted during an established village health and nutrition day camp (held monthly), at the villages within the control group PHC cluster. The community and health professionals will receive information on the high-risk conditions of anaemia in pregnancy, HDP and GDM as part of the awareness programme.

### Stage 3: End of Study Assessment

After the final 6 week postpartum ASHA visit, an independent researcher (not blinded to the intervention) will visit the woman at home and complete an end of study questionnaire, and record BP and Hb readings independently in both the intervention and control groups. This visit will be conducted between 6 and 10 weeks postpartum allowing for convenience of study participants. They will also document if women in the control group had received a 6 week postpartum visit from their ASHA/ANM.

### Primary and Secondary Outcomes

Primary outcomes relating to feasibility of the intervention include:

Recruitment rates of pregnant participants per cluster per month.Retention rates of participants at 6 weeks postpartum.An overview of the acceptability of the SMARThealth Pregnancy intervention using a qualitative sub-study.

Secondary outcomes include:

Prevalence rates of moderate to severe anaemia, HDP and GDM diagnosed in the study sites.Assessment of fidelity of the intervention by:Proportion of visits conducted in line with intervention protocol.Proportion of visits completed by ASHA (including measurement of Hb and BP) at visits during: (a) third trimester, (b) 1–2 weeks postpartum, (c) 6 weeks postpartum, in the intervention group.Proportion of pregnant women detected, referred, managed, and followed-up, with moderate to severe anaemia, HDP or GDM.Proportion of women receiving their 6 week postnatal check by the ASHA.Clinical outcomes: Mean Hb and mean BP at 6 week postpartum visit.

### Process Evaluation

As part of the process evaluation, a qualitative sub-study will be conducted to explore the acceptability of the SMARThealth pregnancy intervention to healthcare workers and pregnant/postpartum women; whether the intervention components had been delivered to plan; how the intervention integrates into existing health system practises; any unintended consequences; and to understand how to improve and refine the intervention and its implementation. A purposive sample of participants including pregnant/postpartum women, CHWs and primary care doctors from the intervention groups at each study site will be invited to share their experiences of the SMARThealth Pregnancy intervention in focus group discussions (FGDs) and/or in-depth interviews (IDIs). We aim to conduct up to four FGDs involving pregnant/postpartum women; up to four FGDs with CHW, and up to four IDIs with primary care doctors across both study sites. Interviews and focus groups will be conducted with CHWs and pregnant/postpartum women at regular intervals during the study: after they have conducted/received visit 1, visit 2 and visit 3; to assess acceptability of each visit to participants as the study progresses. IDIs will be held with doctors at the end of the study to minimise inconvenience due to the workforce constraints affecting primary care doctors in rural areas. Qualitative data from the process evaluation will be analysed using a framework approach (35) using nVIVO QSR^©^ software to facilitate the organisation of the data into codes and categories.

### Statistical Analysis

Analysis of the pilot study will focus on descriptive statistics rather than formal hypothesis testing. Quantitative data relating to the detection, referral, treatment and follow-up rates of pregnant women with (a) anaemia; (b) HDPs; and (c) GDM will be collected for the intervention group. Data relating to the number of pregnant women participating in the study, will allow the proportions of women with these conditions, receiving treatment and follow-up care to be calculated. The proportion of women having their 6 week postpartum visit will also be calculated in both groups. The feasibility of the recruitment strategy and the retention of participants throughout the study will be summarised. Statistical analysis will be conducted at the end of the study once all data collection is completed.

Even though this is a pilot study, we will explore for any differences between the intervention and treatment groups, using an intention-to-treat analysis. Mean differences in 6 week postpartum Hb and BP will be calculated using an analysis of covariance adjusted for the baseline outcome value and for clustering by site. All statistical analysis will be performed using the Statistical Programme for Social Sciences (SPSS^©^).

To inform the sample size calculation for a larger cluster randomised controlled trial, we will calculate the standard deviation around the mean Hb and BP values at 6 weeks postpartum as well as the intra-cluster correlation (ICC) and its 95% confidence interval. ICC estimates will be derived from a mixed-effect model using SAS software^©^.

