## Abstract

**Introduction:** India is in the process of a major epidemiological transition towards non-communicable diseases. Cardiovascular disease (CVD) is the leading cause of death in women in India. Predisposing independent risk factors include pregnancy-related conditions, e.g., hypertensive disorders of pregnancy (HDP) and gestational diabetes (GDM) - also associated with significant perinatal mortality and morbidity. Early identification, referral and management of pregnant women at increased risk of future CVD may offer opportunities for prevention. In rural India, Community Health Workers (CHWs) provide most antenatal and postnatal care. Innovative solutions are required to address integrated care for rural women during transitions between antenatal, postnatal and general health services. The George Institute's SMARThealth Programme has shown that CHWs in rural India screening non-pregnant adults for cardiovascular risk, using a decision support system, is feasible. Building on this, we developed a targeted training programme for CHWs and a complex system-level intervention that uses mobile clinical decision support for CHWs and primary care doctors to screen high-risk pregnant women. In addition to addressing HDP and GDM, the intervention also screens for anaemia in pregnancy.

**Methods/Design:** A pilot study will be undertaken in two diverse rural districts of India: Jhajjar (Haryana) and Guntur (Andhra Pradesh). Two Primary Health Centre clusters will be randomised to intervention or control groups at each study site. The primary objective of this pilot study is to explore the feasibility and acceptability of the SMARThealth Pregnancy intervention. Secondary objectives are to estimate: (a) prevalence rates of moderate to severe anaemia, HDPs and GDM at the study sites; (b) referral and follow-up rates, and (c) mean haemoglobin and blood pressure values at the routine 6 week postnatal visit. A process evaluation will be conducted to explore the acceptability of the SMARThealth Pregnancy intervention for pregnant women and healthcare workers using qualitative methods.

**Discussion:** It is anticipated that the findings of this pilot study will help determine the feasibility and acceptability of the SMARThealth Pregnancy intervention, and highlight how the intervention might be further developed for evaluation in a larger, cluster randomised controlled trial.

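### The Hb and BP ANCOVA adjusts for clustering by site, which in this protocol is the district, while the randomised cluster is the PHC

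*Protocol article*

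**What the plan says.** On allocation, the Randomisation section states: "Randomisation will be at the PHC cluster level". It continues: "Four PHCs (including the villages affiliated to each PHC) will be allocated centrally". The Abstract places these clusters within sites: "Two Primary Health Centre clusters will be randomised to intervention or control groups at each study site". The Process Evaluation section uses the word in the same way: "up to four IDIs with primary care doctors across both study sites". There are two districts, so site is the district and cluster is the PHC. The Participants section gives the size: "We will recruit 200 pregnant women (50 in each of the four PHC clusters) from the two districts".

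The Statistical Analysis section opens with "Analysis of the pilot study will focus on descriptive statistics rather than formal hypothesis testing". It then plans an exploratory, intention-to-treat comparison of 6-week Hb and BP "using an analysis of covariance adjusted for the baseline outcome value and for clustering by site". It mentions no PHC term for this comparison. The ICC and its 95% confidence interval are to come from a separate mixed-effect model.

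**The concern.** In a cluster randomised comparison, the uncertainty of the arm difference is set mainly by variation between the randomised units. The plan adjusts at a level above those units. If each district has one PHC per arm, the arms are compared within district, so a district term removes variation that already cancels from the contrast. PHC variation stays in the contrast and is not modelled.

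This is the only modelled between-arm comparison that the article describes. If its output is shown with the usual standard errors, a chance difference between four PHCs could pass for evidence of an effect on Hb or BP.

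**Working it through.** **Inputs from the protocol.** Four PHCs with 50 women each: 4 × 50 = 200, which reproduces the stated total. There is no power calculation to reproduce.

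**Assumptions.** One PHC per arm in each district, hence two PHCs and 100 women per arm, with no dropout. The ICC, ρ, is taken as 0.01, 0.02 and 0.05. It is the share of the outcome variance left after baseline and district that lies between PHCs. That remaining variance is scaled to 1, and SD below means its square root.

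**Step 1: variance of the arm difference.**
- True variance: 2 × [ρ/2 + (1 − ρ)/100]
- Variance if women are taken as independent: 2 × (1 − ρ)/100
- Ratio: 1 + 50ρ/(1 − ρ)

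This gives 1 + 0.5/0.99 = 1.51, 1 + 1/0.98 = 2.02 and 1 + 2.5/0.95 = 3.63.

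**Step 2: simulation of the literal model.** ANCOVA with arm, district and baseline value, 4 × 50 women, 4,000 trials per ICC:

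| ICC | Variance ratio (formula) | True SE / reported SE (simulated) | Coverage of nominal 95% interval |
|---|---|---|---|
| 0 | 1.00 | 0.98 | 95% |
| 0.01 | 1.51 | 1.21 | 90% |
| 0.02 | 2.02 | 1.42 | 83% |
| 0.05 | 3.63 | 1.89 | 70% |

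The squared SE ratios (about 1.5, 2.0 and 3.6) agree with the formula. In the same simulations, a paired analysis of PHC means on 1 df held about 95% coverage throughout.

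**Step 3: degrees of freedom.** The individual-level model uses 200 − 4 = 196 df (t = 1.97). Four PHC means leave 4 − 2 = 2 df with arm fitted (t = 4.30), or 4 − 3 = 1 df with arm and district fitted (t = 12.71).

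- ICC 0.05: true SE = √0.069 = 0.263 SD; mean reported SE = 0.139 SD. Half-widths are 1.97 × 0.139 = 0.27 SD (individual level), 4.30 × 0.263 = 1.13 SD (2 df) and 12.71 × 0.263 = 3.34 SD (1 df).
- ICC 0.01: true SE = √0.0298 = 0.1726 SD; mean reported SE = 0.141 SD. Half-widths are 0.278, 0.74 and 2.19 SD. The PHC-level interval is thus about 2.7 to 7.9 times as wide.

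**Step 4: would another handling of PHC work?** If PHC is entered as a fixed covariate, arm is the sum of the indicators of the two intervention PHCs, so the arm effect is not estimable. A random PHC intercept is estimable in principle. With arm and district fitted, however, it estimates the PHC variance from 1 df. The chance that this estimate is zero or negative is about P(χ² on 1 df < (1 − ρ)/(1 + 49ρ)). The thresholds are 0.664, 0.495 and 0.275, giving about 58%, 52% and 40% at ICC 0.01, 0.02 and 0.05. A fit constrained at zero then falls back to the model that ignores PHC.

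**The case against.** **No interval or test is promised for the mean differences.** The section calls the analysis descriptive, and its only stated confidence interval is for the ICC. This stands. A reader might infer that the trial will publish intervals that are far too narrow, but the text does not commit to that. The problem arises when an SE, interval or p-value is shown, as ANCOVA output usually does. With equal PHC sizes and one PHC per arm in each district, the wording also does not bias the point estimate.

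**Clustering may have been meant as PHC, handled by a random effect or a cluster-adjusted variance.** Cluster does mean PHC elsewhere, so this reading is possible. A reader might infer that the model fails however it is read. That goes too far, because a random PHC effect is estimable, though unreliable with four clusters. What does not stand is that this is a detail for the SAP: the sentence names a level, and by the protocol's own usage it is the wrong one.

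**The consequence is limited.** The primary outcomes are recruitment, retention and acceptability, and none of them uses this ANCOVA. A reader might infer that a spurious difference would feed into the definitive trial. However, the inputs named for that sample size calculation are the SD and the ICC, and nothing says that the arm difference will set the target effect. This stands and lowers the severity.

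**The size depends on an ICC that the protocol does not give.** This is true. At 0.01 the SE alone is about 18% too small (1 − 1/1.22), and most of the widening comes from the 1 to 2 df. At an ICC of 0, the individual-level coverage would be correct.

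**Conclusion.** The point holds as an error in a stated rule: the comparison is adjusted for the district although the PHC is the randomised unit. With district as a term in the ANCOVA, any measure of precision attached to the Hb and BP differences is too tight for every ICC above 0. Under the assumed ICCs of 0.01 to 0.05, the variance is understated about 1.5 to 3.6 times and coverage is about 90% down to 70%. Counting PHC-level df widens the interval further.

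These figures assume 50 analysed women per PHC and one PHC per arm in each district. The Abstract points to that layout. The Randomisation section, though, describes simple random allocation of four PHCs and states no restriction by district. If two of the four were chosen for intervention without restriction, both would lie in one district in 2 of 6 possible choices, and site and arm would then be confounded.

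Because the comparison is exploratory and the primary outcomes are feasibility measures, this is a should-fix.

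**What to change.** In the Statistical Analysis section:

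- Replace clustering by site with the PHC as the cluster and district as a stratum.
- Analyse baseline-adjusted PHC-level means. Do not rely on a random PHC intercept with four clusters.
- Report the four adjusted PHC means and, where each district has one PHC per arm, the two within-district differences. Present them descriptively, without p-values.
- Base any interval on PHC-level df, and state that four clusters cannot support a useful interval.

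The cost is a change of wording. Data collection and design are unaffected. Any interval becomes much wider, and that width reflects what four clusters can show.

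### The exploratory Hb and BP ANCOVA has no timing term, although the baseline reading can fall anywhere in an 8-week window and the outcome reading anywhere in a 4-week window

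*Protocol article*

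**What the plan says.** The Statistical Analysis section makes the pilot mainly descriptive but adds an exploratory intention-to-treat comparison of the arms: "Mean differences in 6 week postpartum Hb and BP will be calculated", using "analysis of covariance adjusted for the baseline outcome value and for clustering by site". Those are the only adjustments named.

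The timing of the two readings is set elsewhere in the protocol:

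- **Baseline.** Under Participants, women are "between 28 and 36 weeks' gestation, and followed up until and including 6 weeks postpartum". Under Recruitment and Consent, BP and Hb are "measured at home by an independent member of the research team at the baseline of the study". That reading has no gestational week of its own, so its range is inferred from the enrolment window.
- **Outcome.** Under Stage 3: End of Study Assessment, an independent researcher reads BP and Hb in both groups: "This visit will be conducted between 6 and 10 weeks postpartum allowing for convenience of study participants". The analysis section nevertheless labels the outcome as a six-week value.

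On allocation and size: "Randomisation will be at the PHC cluster level" and "We will recruit 200 pregnant women (50 in each of the four PHC clusters) from the two districts". The Abstract has two PHCs randomised in each district, read here as two per arm overall. Study Design calls the trial unblinded.

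**The concern.** Hb and BP may be expected to change through the third trimester and again in the weeks after birth. If they do, a baseline value at 28 weeks does not carry the same information as the same value at 36 weeks, and an outcome at 6 weeks is not on the same footing as one at 10 weeks. Adjusting for the baseline value and for clustering removes neither difference.

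Two features leave the balance of timing unprotected. First, there are probably two PHCs per arm, so differences between PHCs in when women are enrolled or visited have little chance to average out. Second, what women are asked to consent to differs by arm, which implies that allocation is known when each woman is recruited. The ANMs who identify eligible women receive the full training programme in the intervention arm and an awareness programme in the control arm. The end reading follows a scheduled ASHA study visit in one arm and the routine postnatal visit in the other.

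At stake are the early estimates of difference in Hb and BP, which could carry a component that reflects calendar rather than intervention.

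**Working it through.** **Plan's own figure.** 4 PHCs × 50 women = 200, as stated. There is no power-based sample size to reproduce.

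**Windows.** Baseline: 36 − 28 = 8 weeks. Outcome: 10 − 6 = 4 weeks.

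**Assumed inputs (none is in the protocol).** Hb drift 0.05 to 0.20 g/dL per week; Hb SD 1.5 g/dL; ANCOVA coefficient on baseline 0.5; ICC 0 to 0.10; SD of PHC mean timing 0.5 to 1.0 week. The independent home readings are taken as baseline and outcome, since both arms have them. No drift was assumed for BP, so no size is given for it.

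**Step 1: how large a timing imbalance is plausible?** A uniform spread over a window of width W has SD W/√12: 8/√12 = 2.31 weeks and 4/√12 = 1.15 weeks. With 100 women per arm and no PHC effect on timing, the arm difference in mean timing has SD equal to this times √(2/100): 0.33 week at baseline and 0.16 week at outcome. If PHC means vary with SD s and there are two PHCs per arm, the SD becomes √(s² + 0.33²) or √(s² + 0.16²). For s = 0.5 to 1.0 week that gives 0.60 to 1.05 weeks and 0.53 to 1.01 weeks. An imbalance of 0.5 to 1 week is therefore a reasonable working range.

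**Step 2: shift in the Hb difference.**

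- Outcome timing: imbalance × drift, from 0.5 × 0.05 = 0.025 to 1 × 0.20 = 0.20 g/dL.
- Baseline timing: −0.5 × imbalance × drift, from 0.5 × 0.5 × 0.05 = 0.013 to 0.5 × 1 × 0.20 = 0.10 g/dL in size, opposite in sign for a later reading.
- Either one: about 0.01 to 0.20 g/dL. If both pushed the same way, at most 0.20 + 0.10 = 0.30 g/dL.

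**Step 3: compare with the comparison's uncertainty.** SE = SD × √[(2/100)(1 + 49 × ICC)].

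| ICC | Design effect | SE (g/dL) | 95% half-width, normal | 95% half-width, t on 2 df |
|---|---|---|---|---|
| 0 | 1.00 | 0.21 | 0.42 | 0.91 |
| 0.01 | 1.49 | 0.26 | 0.51 | 1.11 |
| 0.05 | 3.45 | 0.39 | 0.77 | 1.70 |
| 0.10 | 5.90 | 0.52 | 1.01 | 2.22 |

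These use the raw SD. At ICC 0, baseline adjustment with a correlation of 0.5 multiplies the half-width by √(1 − 0.25) = 0.87, so 0.42 becomes 0.36. The shifts in Step 2 remain inside it.

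**Step 4: bias or noise?** Allocation within district was simulated with a PHC timing SD of 0.5 week and a drift of 0.1 g/dL per week. The shift averaged about 0 with SD 0.05 g/dL. Timing that does not depend on arm therefore adds noise over repeated randomisation; it becomes systematic only if recruitment or visit timing depends on arm.

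**Step 5: effect on the SD.** At the steepest drift, timing spread within the outcome window adds 0.20 × 1.15 = 0.23 g/dL in quadrature: √(1.5² + 0.23²) = 1.52, a rise of 1.2%. At 0.05 g/dL per week the rise is under 0.1%.

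**The case against.** The case against is substantial. This is a condensed article, the SAP is not shown, and further covariates for an exploratory comparison are ordinary SAP content. ANCOVA on the baseline value with allowance for clustering is a standard choice. Both arms share the same windows, and the assumed shifts are small against a comparison of two PHCs with two. All of this stands, and it keeps the weight low. It does not remove the point, because the article states its adjustment set and also sets two wide windows that the set ignores.

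A reader might infer more than the protocol supports:

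- **That the model adjusts for the baseline value only.** It also allows for clustering by site. What it lacks is any timing variable.
- **That timing differs between arms and so biases the result.** Nothing in the protocol shows this. The different anchors of the end visit and the unblinded recruitment leave a route open, no more. Without arm dependence, the effect is chance imbalance.
- **That the distortion could reach 0.55 g/dL.** This needs opposite 2-week imbalances at both ends and drifts of 0.15 and 0.20 g/dL per week: 0.5 × 0.15 × 2 + 0.20 × 2 = 0.55. Two weeks is about 6 SDs (2/0.33) and 12 SDs (2/0.16) of the imbalance expected without PHC differences. Even with a PHC timing SD of 1.0 week, such a pair has a probability of roughly 0.1%.
- **That the definitive trial's SD is compromised.** The section plans a raw SD and an ICC from a mixed model, not the ANCOVA residual SD, and Step 5 puts the effect on the SD at about 1% or less.

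A last objection also stands: weeks postpartum is observed after allocation. If visit timing does depend on arm, adjusting for it in the main model is contestable.

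**Conclusion.** The concern holds as a modest one. The stated Hb and BP model omits timing although the protocol allows 8 weeks of variation at baseline and 4 weeks at outcome. With four PHCs and individual recruitment into an unblinded trial, timing differences can enter the arm difference. For Hb the likely size is about 0.01 to 0.20 g/dL for a 0.5 to 1 week imbalance, below the comparison's own 95% half-width. This rests on assumed drift, SD, ANCOVA coefficient, ICC and PHC timing spread. If Hb and BP do not drift over these windows, there is no shift. No size is claimed for BP. The case for acting is that gestational age is already needed for eligibility, so the better model costs almost nothing.

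**What to change.** In the Statistical Analysis section, or in the SAP if it does not already do so:

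1. Add gestational age in weeks at the baseline reading as a covariate in the ANCOVA for Hb and for BP.
2. Tabulate gestational age at the baseline reading and weeks postpartum at the independent end-of-study reading, by PHC and by arm, so that any imbalance can be seen.
3. Report a sensitivity analysis that also adjusts for weeks postpartum, labelled as adjustment for a post-allocation variable. Keep it out of the main model.
4. Keep the planned raw SD and the ICC as the inputs to the definitive trial. Show an adjusted SD only as a supplement, since it suits only a trial that makes the same adjustment.

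The cost is a sentence or two of text, one degree of freedom in the main model and two in the sensitivity model, and one extra result to report. Gestation is known from eligibility, and time since birth is needed to place the end visit in its window, so no new data collection is implied.
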